## Abstract

**Background:**

Preoperative carbohydrates (CHO) supplement has been widely investigated in nondiabetic patients undergoing a variety of surgeries. It has been proved that preoperative CHO could alleviate postoperative insulin resistance (IR) and improve patients’ well-being in nondiabetic patients. However, it remains controversial whether preoperative CHO could yield similar effects in diabetic patients. Till now, seldom has the administration of preoperative CHO been investigated in diabetic patients and there are limited studies reporting IR and postoperative recovery of diabetic patients undergoing cardiac surgery.

**Methods and analysis:**

We present a prospective, single-center, single-blind, randomized, no-treatment controlled trial of preoperative CHO on diabetic patients undergoing off-pump coronary artery bypass grafting (OPCAB). A total of 62 patients will be enrolled and randomized to either Group CHO or Group control (CTRL). Patients in Group CHO will consume CHO fluid containing 50 g carbohydrates orally the evening before surgery (20:00–24:00) while their counterparts in Group CTRL will be fasted after 20:00 the evening before surgery. The primary endpoint is postoperative IR assessed via homeostasis model assessment (HOMA). The secondary endpoints are postoperative levels of potential mediators relating to IR including inflammatory factors and stress reaction characterized by serum cortisol. Exploratory endpoints are in-hospital clinical endpoints. Continuous variables will be compared by Student’s *t*-test or Mann-Whitney *U* test. Categorical variables will be compared with *χ*^2^ test or Fisher’s exact test. All tests in the present study are two-tailed and *P*<0.05 is considered statistically significant. All analyses will be performed with R 4.0.4.

**Discussion:**

This is the first prospective randomized controlled trial of preoperative CHO in diabetic patients undergoing cardiac surgery, with the hypothesis that preoperative CHO could improve postoperative IR and promote postoperative recovery. The research may assist in improving the clinical outcomes of diabetic patients undergoing OPCAB.

**Trial registration:**

The trial has been prospectively registered with ClinicalTrials.gov (https://register.clinicaltrials.gov) and Chinese Clinical Trial Registry (http://www.chictr.org.cn). Registry number is NCT05540249 and ChiCTR2000029664 respectively. Registered on Sept. 14, 2022.

**Supplementary Information:**

The online version contains supplementary material available at 10.1186/s13063-022-07042-w.

## Background

Introduced by a group of European surgeons in 2001, the Enhanced Recovery After Surgery (ERAS) program, as a paradigm shift in perioperative care, has been widely implemented in several surgical subspecialties [1]. Optimizing preoperative fasting protocol is one of the critical elements in the ERAS program. Traditional surgery often requires 8–12 h of preoperative fasting to reduce the risk of pulmonary aspiration of gastric contents. However, it has been proved that fasting leads to a catabolic metabolic state characterized by increased insulin resistance (IR) and post-operative stress reaction [2]. Meanwhile, fasting causes patient discomfort and may be associated with poor clinical outcomes. To ameliorate the deleterious effects caused by the preoperative fasting, the ERAS protocol recommends preoperative oral carbohydrates (CHO) loading for patients undergoing surgery, adults and children alike [3]. Previous study illustrated that the intake of CHO 2 to 3 h before elective colorectal surgery could reduce postoperative IR [4]. Similar effects have also been recognized in other surgeries, such as hepatic surgery [5], hip replacement surgery [6], and cholecystectomy [7].

The prevalence of diabetes mellitus (DM) in Chinese mainland has been increasing these years and is now approximately 12.8% [8]. IR plays a pivotal role in the initiation and development of type 2 diabetes mellitus (T2DM) [9]. Typically, IR is defined as decreased sensitivity or responsiveness to the metabolic effects of insulin [10]. Evidence has suggested that IR could hinder recovery postoperatively and prolong the length of hospital stay [11, 12]. Notably, the degree of postoperative IR is more pronounced after major surgeries than the minor ones [13]. Cardiac surgery represents a typically invasive intervention with a protracted recovery phase that often requires intensive rehabilitation and postoperative pain management. T2DM is a well-established risk factor of coronary artery disease and as much as 20% - 30% of patients undergoing coronary artery bypass grafting are complicated with T2DM [14]. Thus, it is of great significance to investigate the best ERAS protocol for T2DM patients referred to coronary surgery.

The benefits of preoperative CHO in nondiabetic patients have been well-established. In contrast, it remains controversial whether preoperative CHO supplement could yield similar effects in T2DM patients. Till now, the administration of preoperative CHO in T2DM patients has been seldomly investigated and there are limited studies reporting IR and postoperative recovery of diabetic patients undergoing cardiac surgery. Therefore, we put forward the present protocol to introduce a randomized controlled trial examining the impact of preoperative oral CHO on IR and postoperative recovery in T2DM patients undergoing off-pump coronary artery bypass grafting (OPCAB).

## Methods and analysis

### Objectives

The trial is designed to assess the effects of preoperative CHO in T2DM patients undergoing OPCAB. The main hypothesis is that preoperative CHO has advantages in improving postoperative IR and promoting postoperative recovery in T2DM patients undergoing OPCAB. The primary objective is to determine the efficacy of preoperative CHO in improving postoperative IR. The secondary objective is to assess the postoperative level of potential IR-related mediators including biochemical parameters, inflammatory mediators, and stress reaction. In the explorative study, the effects of preoperative CHO on postoperative recovery will be investigated. Postoperative recovery could be assessed via postoperative clinical outcomes such as nausea or vomiting, perioperative myocardial injury or infarction, chest tube drainage, mechanical ventilation time, ICU length, and hospital stay.

### Study setting and trial design

The present study is a single-center, single-blind, randomized controlled trial. The study protocol has been approved by the Ethics Committee of Fuwai Hospital (No. 2019-1301) and has been registered with ClinicalTrials.gov (https://register.clinicaltrials.gov) and Chinese Clinical Trial Registry (http://www.chictr.org.cn) prospectively. Registry number is NCT05540249 and ChiCTR2000029664 respectively.

The relevant data of T2DM patients admitted to the cardiovascular ward will be collected prospectively and consecutively from the electronic medical system. The study will be carried out under strict supervision based on our center’s fasting routine before surgery. Included patients will be randomized into one of the two groups: the control group (Group CTRL) and the preoperative CHO group (Group CHO). The surgeons, anesthesiologists, intensive care unit (ICU) staff, nurses, outcome assessors, data collectors, and data analysts will be blinded to patient grouping. This study is structured according to the 2013 Standard Protocol Item Recommendations for Interventional Trials (SPIRIT) guideline [15] defining standard protocol items for clinical trials and the SPIRIT checklist has been completed (seen in Additional file).

### Eligibility criteria

Trial eligibility criteria will be applied strictly to enroll those T2DM patients undergoing OPCAB. As the cardiopulmonary bypass (CPB) could elicit substantial metabolic changes [16], all included patients will be operated without CPB. As some hormones may affect the IR, we will exclude patients on preoperative hormonal drugs due to endocrine system disease such as thyroid or adrenal dysfunction. All qualified patients will be fully informed of the trial procedures and provide the written informed consent. The detailed eligibility criteria are listed in Table 1.

**Table 1 Tab1:** Eligibility criteria

Inclusion criteria	
1. Previously diagnosed T2DM 2. Diagnosed with CAD with coronary angiography and indicated for OPCAB 3. Age between 18 and 75 years old 4. First operation in the morning and anesthesia induced around 8:00 5. Written informed consent by the patients	
Exclusion criteria	
1. Combined with other heart diseases or vascular malformations that require surgery in addition to OPCAB 2. Presence of symptoms or signs of heart failure such as orthopnea, distended jugular vein, and lower extremity edema 3. Reduced LVEF (lower than 50%) 4. Combined with gastroesophageal reflux 5. Combined with thyroid insufficiency requiring replacement therapy with levothyroxine 6. Combined with adrenal insufficiency requiring replacement therapy with corticosteroids 7. Refuse to participate.	

*T2DM* type 2 diabetes mellitus, *CAD* coronary artery disease, *OPCAB* off-pump coronary artery bypass graft, *LVEF* left ventricular ejection fraction

### Patient and public involvement statement

While designing the study, we visited an in-hospital DM patient ready to receive the OPCAB. With the assistance of study staff, he reviewed the original study protocol and engaged in discussing about the amendment and optimization of the study protocol.

### Grouping and allocation concealment

Patients meeting the eligibility criteria will be randomized to either the Group CHO or the Group CTRL. The carbohydrates beverage Outfast® (Yichang Humanwell Pharmaceutical Co., Ltd., China) used in the study, is isotonic with osmotic pressure of 280–320mmol/L and PH of 3.8–4.3. Patients in Group CHO will orally consume CHO 355ml containing 50 g of carbohydrates 8–12 h before operation (20:00–24:00 the evening before operation). In order to improve adherence to intervention protocol, patients in the Group CHO will be asked to return the empty beverage bottle to the investigator after drinking the beverage. The Group CTRL will consume no food or drink 12 h before operation (20:00 the evening before operation). Based on the random numbers generated by the computer, qualified patients will be randomized to the Group CHO or Group CTRL the day before surgery. The random number list will be kept in the hand of a dedicated person who will assign participants to Group CTRL or Group CHO according to the random numbers. The surgeons, anesthesiologists, ICU staff, nurses, outcome assessors, data collectors, and data analysts will be blinded to the grouping. Unblinding is permissible when patients suffer from gastric acid reflux and aspiration.

### Anesthesia induction, maintenance, and surgical procedures

Invasive blood pressure will be monitored continuously via the left radial artery once the patients’ arrival at the operating room. Before anesthesia induction, gastric emptying will be assessed with a Philips CX50 ultrasound system equipped with a C5-1 abdominal transducer. The cross-sectional area of the stomach antrum will be measured in the supine position. The image of the stomach antrum will be acquired in the parasagittal plane of the epigastric area.

Anesthesia induction and maintenance will be practiced in a standard manner in all eligible patients. Anesthesia induction consists of a combination of sufentanil 2 μg/kg, midazolam 0.1 mg/kg, etomidate 0.2 mg/kg, and cis-atracurium besylate 0.15 mg/kg. Anesthesia will be maintained with propofol 2 mg/kg/h, dexmedetomidine 0.5 μg/kg/h, cis-atracurium besylate 0.1 mg/kg/h, and sevoflurane 1%. The intraoperative anesthesia management in our center has been previously described in detail [17]. All patients will undergo OPCAB, and the procedures will be performed by the experienced surgeons who have ever performed more than 500 OPCABs. Left internal mammary artery (LIMA) will be routinely grafted to the left anterior descending artery (LAD), and other lesioned coronary arteries will be grafted by single or sequential saphenous vein grafts (SVG). Sometimes radial artery will be harvested if SVG is in poor condition and not suitable for grafting.

### Blood glucose monitoring and management

In this study, the target of glycemic control will be set at 7.8–10 mmol/L.

Blood glucose will be routinely measured every hour during surgery and every 2 h in the ICU after surgery. The blood glucose threshold of initiating insulin therapy will be set at 10.0 mmol/L for the critically ill patients in the ICU. If the blood glucose is beyond 10 mmol/L but below 12.2mmol/L, a bolus dose of 2–4U insulin will be administered intravenously and the initial maintaining rate will be set at 2U/h. If the blood glucose is beyond 12.2mmol/L but below 16.7mmol/L, a bolus dose of 4–6U insulin will be administered intravenously and the initial maintaining rate is set at 4U/h. If the blood glucose is beyond 16.7mmol/L, a bolus dose of 6–8U insulin will be administered intravenously and the initial maintenance rate is set at 6U/h. If the blood glucose continues to rise, the infusion rate will be raised with the increment of 2U/h. If the blood glucose decreases by more than 25%, the rate of intravenous insulin infusion will be reduced with the decrement of 2U/L. If the blood glucose is less than 5.6 mmol/L, 20–40mL 50% glucose solution will be intravenously infused to restore the blood glucose to 7.8–10 mmol/L.

After patients return to the surgical ward, fingertip blood glucose will be routinely measured four times a day, that is, fasting blood glucose in the morning and 2 h after three meals. As patients have resumed regular diet, glycemic management will be turned to preoperative medical protocol, whether oral hypoglycemic drugs, insulin, or both. If the blood glucose rises sharply beyond 10.0mmol/L, extra insulin will be administered percutaneously to restore the blood glucose to the target level.

### Data collection, management, and monitoring

A well-designed questionnaire will be applied to collect the baseline characteristics of eligible patients. Two to 3 persons will be trained to assist in collecting baseline characteristics including demographical data and medical history. The results of blood tests will be obtained from the digital medical record system. A dedicated person will record all the data in an excel sheet and no one else will have access to the data in the excel sheet until statisticians analyze the collected data at the end of the study. As the intervention in the present study is low-risk and unlikely to cause severe complications to patients, the Independent Data Monitoring Committee is not considered.

### Quality control

Before the enrollment of the first patient, all participants in the trial including surgeons, anesthesiologists, ICU staff, nurses, outcome assessors, data collectors, and data analysts shall receive unified training to be familiar with the detailed process of the trial. This trial steering committee (TSC) is composed of the chief supervisor and five members with more than 5-year experience in clinical trial. With the assistance of the five members, the chief supervisor shall organize meetings to discuss problems in the process of the trial every 2 weeks and oversee the conduct and progress of the trial. The five members shall coordinate the work of involved departments and provide the necessary support for the trial.

### Statistical analysis

Modified intention-to-treat analysis is adopted to analyze the data. If the operation of an enrolled patient is canceled due to special circumstances such as fever, the random number will be reserved to him/her until the end of the trial. If the patient whose operation is canceled contemporarily is operated later before the end of the trial, he/she will be assigned to the Group CTRL or Group CHO according to the early-assigned random number. If the patient who doesn’t undergo the operation as planned is not operated before the end of the trial or whose operation is rescheduled to a later time of the day instead of the first operation at 8’oclock, he/she will be excluded from the trial and extra random number will be generated to enroll enough patients to the prespecified sample size.

The primary endpoints, homeostasis model assessment (HOMA) of IR, will be compared between the two groups at several fixed time after surgery. In addition, overall postoperative IR will be assessed via area-under-curve of HOMA (AUC_HOMA_) and AUC_HOMA_ will be compared between the two groups. The secondary endpoints, postoperative IR-related mediators, will be compared between the two groups primarily at the first morning after surgery. In the exploratory study, in-hospital outcomes as listed in the following part of the study endpoints will be compared between the two groups. Normal distribution of continuous variables will be tested using the Shapiro-Wilks test. Continuous variables will be presented as mean ± standard deviation if the variables follow a normal distribution, otherwise median and interquartile range. Categorical variables will be presented as number and percentage. Missing data will be managed via multiple imputation. Continuous variables with normal distribution will be compared by Student’s *t*-test between the groups. Continuous variables with skewed distribution will be compared by Mann-Whitney *U* test. We will compare categorical variables with the *χ*^2^ test or Fisher’s exact test. The Spearman rank correlation test will be utilized to assess the correlation between continuous variables.

The analysis will be performed by a dedicated data analyst who is masked to subjects’ group allocation. All the tests in the present study are two-tailed and *P*<0.05 is considered statistically significant. All analyses will be performed with R 4.0.4 (R Foundation for Statistical Computing, Vienna, Austria).

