### Sample size calculation

The primary outcome is the postoperative IR assessed *via* HOMA of the function of islet β cell (HOMA-β). Previous literature [18] showed that the HOMA-β of the CHO group tended to be higher than that of the F group-β (87% *vs*. 47.5%). In the present study, the test power was set to 0.80, two-sided α was set to 0.05, and the dropout rate was set to 0.1. It was estimated that a total of 62 patients with 31 patients in group CHO and 31 patients in group C would be enrolled.

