## Study endpoints

### Primary endpoints

The primary endpoints are postoperative HOMA-β and HOMA-IR. HOMA score is a mathematical model that can reflect the balance between liver glucose output and insulin secretion, and it has been previously demonstrated that it has a strong correlation with clamp-measured total glucose disposal, the gold standard of assessing IR [19].

The calculation formulas of HOMA-β and HOMA-IR are as follows:

$$\textrm{HOMA}-\upbeta \%=\left[20\times \textrm{fasting}\ \textrm{insulin}\ \left(\textrm{mu}/\textrm{L}\right)\right]/\left[\textrm{fasting}\ \textrm{blood}\ \textrm{glucose}\ \left(\textrm{mmol}/\textrm{L}\right)-3.5\right]\%$$$$\textrm{HOMA}-\textrm{IR}=\left[\textrm{blood}\ \textrm{insulin}\ \left(\textrm{mu}/\textrm{L}\right)\times \textrm{Blood}\ \textrm{glucose}\ \left(\textrm{mmol}/\textrm{L}\right)\right]/22.5$$

The HOMA-β is expressed as percentage, and its normal value is 100%. The HOMA-IR is expressed without unit, and its normal value is 1. With the increase of IR, the HOMA-β will be lower than normal and the HOMA-IR will be higher than normal.

The baseline HOMA-β and HOMA-IR will be acquired at admission. And then these two HOMA scores will be sequentially measured before anesthesia induction, immediately after surgery, the first morning after surgery (POD1), POD2, POD 3, and POD 5 (Fig. 1)

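### No single test decides the primary question: one or two HOMA scores, five postoperative times and an AUC are all judged at P<0.05, so the stated 5% error rate is not delivered

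*Protocol article*

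**What the plan says.** Four parts of the protocol article bear on the point.

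- **Primary endpoints:** "The primary endpoints are postoperative HOMA-β and HOMA-IR". After the admission and pre-induction samples, the postoperative samples are taken "immediately after surgery, the first morning after surgery (POD1), POD2, POD 3, and POD 5", which is five times.
- **Statistical analysis:** "The primary endpoints, homeostasis model assessment (HOMA) of IR, will be compared between the two groups at several fixed time after surgery". The section then brings in a summary measure across these times: "overall postoperative IR will be assessed via area-under-curve of HOMA", and that area is also compared between groups. The section closes with a general rule: "All the tests in the present study are two-tailed", with P<0.05 counted as significant. The Abstract repeats the rule. No adjustment, hierarchy or leading time point is given for the primary endpoints.
- **Sample size calculation:** "The primary outcome is the postoperative IR assessed *via* HOMA of the function of islet β cell (HOMA-β", a single score with no time point. It is planned at two-sided α 0.05, power 0.80 and 10% dropout, for 62 patients.
- **Objectives:** "The main hypothesis is that preoperative CHO has advantages in improving postoperative IR and promoting postoperative recovery in T2DM patients undergoing OPCAB". The same section then assigns recovery to an exploratory study.

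**The concern.** A stated α of 0.05 means something only if the reader knows which test it belongs to. The sample size budgets α for one comparison, but the analysis section provides for up to twelve, each with the full 0.05, and does not say which one answers the primary question. A significant result at one time on one score could be presented as the trial's primary result, and the protocol would give no ground for disputing it.

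The two scores make the choice matter more. Insulin is in the numerator of both formulas, so a chance rise in insulin tends to raise both. Yet the Primary endpoints section reads a higher HOMA-β as better and a higher HOMA-IR as worse. Chance movement in either direction can therefore look favourable on one of them.

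**Working it through.** **Inputs from the protocol article**

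- Primary scores: two (Primary endpoints) or one (Sample size calculation).
- Postoperative times: five (Primary endpoints).
- AUC: one comparison per score. The Statistical analysis section does not say which score the AUC uses, or over what window.
- Level: two-sided 0.05 per test (Statistical analysis).
- Evaluable patients: 31 × 0.9 ≈ 28 per arm (Sample size calculation).

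**The plan's own figure.** The 62 patients cannot be reproduced, because the HOMA-β means (87% and 47.5%, difference 39.5 points) come without an SD. Taken as a comparison of means, 62 needs an assumed SD of about 51–52 points. For SD 52, n = 2 × (1.96 + 0.84)² × 52² / 39.5² ≈ 27.2, so 28 per arm; 28 × 1.1 = 30.8, so 31. For this point, what matters is that the calculation covers one test of HOMA-β.

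**Number of tests**

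- Two scores: 2 × (5 + 1) = 12, or 11 if only one AUC is meant.
- One score: 5 + 1 = 6.

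**Reference value under independence**

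- 12 tests: 1 − 0.95¹² = 0.460
- 6 tests: 1 − 0.95⁶ = 0.265

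The AUC is built from the five times and repeated measures are correlated, so the real rates lie below these values.

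**Simulation under no effect, with assumed correlations.** 28 per arm, t-tests, trapezoidal AUC, 20,000 runs per setting. The rows below use equal correlation between all times.

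| Correlation between times | Correlation between scores | At least one P<0.05, 12 tests | At least one P<0.05, 6 tests |
|---|---|---|---|
| 0.01 | 0 | 42.7% | 24.5% |
| 0.3 | 0.5 | 36.7% | 21.9% |
| 0.5 | 0.5 | 31.7% | 18.7% |
| 0.7 | 0.5 | 25.6% | 14.8% |
| 0.9 | 0.9 | 13.7% | 10.0% |

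Correlation that decays with distance in time gave rates within the same overall range.

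**Simulation with the protocol's HOMA formulas and test choice.** Shapiro-Wilk, then t or Mann-Whitney; in the main set-up, log-normal insulin with SD 0.6 on the log scale and glucose 9 ± 1.5 mmol/L were assumed. Over repeated runs, 12 tests gave 32–34%, 30–32% and 23–25% at between-time correlations 0.3, 0.5 and 0.7, and 15% at 0.9. One score alone gave 9–23%.

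**Direction.** Counting only results in favour of carbohydrate (higher HOMA-β or lower HOMA-IR), the 12-test rate was about 13–22%. The matching one-direction benchmark is 2.5%.

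**If all 12 tests were kept.** Bonferroni needs 0.05/12 = 0.0042 per test. An effect with 80% power at 0.05 would then have power Φ(1.96 + 0.84 − 2.87) = Φ(−0.06) ≈ 47% per test.

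**The case against.** **This belongs in an analysis plan that is not shown.** Multiplicity procedures are often left there, and an article condenses. But this article states the rule itself: every test at P<0.05. It also names a leading time where one was wanted, since the mediators are compared primarily on the first morning after surgery. The primary endpoints have no such statement. A separate plan would have to override the published text and settle the conflict over one or two primary endpoints.

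**The count of 12 is only one reading.** This stands. If the Sample size calculation section governs, HOMA-β alone is primary and the family is six. That lowers the rate but still leaves no deciding time.

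**The size rests on assumptions.** This also stands. A reader might infer one multiplier, such as five to six times the stated error. The document gives no SDs or correlations, so only a range can be supported, and it narrows towards 5% as the correlations approach 1.

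**Not every false positive favours carbohydrate.** Correct. A reader might take 14–46% as the chance of a false claim of benefit. The tests are two-sided, so it is not. The directional rates are lower, though still well above 2.5%.

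**The exploratory outcomes.** A reader might extend the argument to the many in-hospital outcomes and put a figure on them. The article labels them exploratory, and many are binary, where Fisher's test can fall well below its nominal level. No such figure is claimed here. The remaining issue is that recovery sits in the main hypothesis while only exploratory outcomes address it.

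**Conclusion.** The concern holds in this form: the article names no deciding primary test, contradicts itself on whether there is one primary endpoint or two, and applies an unadjusted 0.05 to every comparison. With no true effect, at least one primary test is significant in about 14–46% of trials on the 12-test reading (46% being the independence value) and in about 9–26% on the six-test reading, against the stated 5%. These ranges rest on assumed correlations and, in some runs, assumed insulin and glucose distributions. No setting tried came close to 5%. The structural defect rests on the text alone. It should be corrected, because the trial's one confirmatory claim has no defined test.

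**What to change.** Before enrolment, reconcile the Primary endpoints, Statistical analysis and Sample size calculation sections. The Trial status section says enrolment had not begun at submission.

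1. Name one deciding test at two-sided 0.05: one HOMA score, and either one time point or the postoperative AUC with its window stated.
2. Make it match the sample-size basis. Either keep HOMA-β, the only score with a design effect, and state its time point or AUC window, or choose another. If HOMA-IR or an AUC is chosen, restate the design effect, the SD and the power that 62 patients give for it.
3. Report the other score, the other times and the remaining comparisons as supportive estimates with 95% confidence intervals.
4. In Objectives, present recovery as an exploratory aim and not as part of the main hypothesis.

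**Cost.** Keeping HOMA-β at a named time is largely a matter of wording. Moving to HOMA-IR or an AUC also requires a new sample-size justification. In either case, a difference confined to another time point or the other score can no longer be claimed as confirmatory.

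### A normality pre-test on the trial data chooses between t-test and Mann-Whitney for each variable, so the effect measure of the primary HOMA endpoints is not fixed in advance

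*Protocol article*

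**What the plan says.** All the rules are in the protocol article, Statistical analysis section.

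- Pre-test: "Normal distribution of continuous variables will be tested using the Shapiro-Wilks test". No significance level is given, and it is not said whether the test is run within each arm or on both arms together.
- If it passes: "Continuous variables with normal distribution will be compared by Student’s *t*-test between the groups".
- If it fails: "Continuous variables with skewed distribution will be compared by Mann-Whitney *U* test".
- The summary switches on the same result: "mean ± standard deviation if the variables follow a normal distribution, otherwise median and interquartile range".
- The primary HOMA endpoints "will be compared between the two groups at several fixed time after surgery", and also as an area under the curve. No other model is named for them.
- In the same paragraph: "Missing data will be managed via multiple imputation".

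The Primary endpoints section names two scores, HOMA-β and HOMA-IR. Its postoperative measurement times are "immediately after surgery, the first morning after surgery (POD1), POD2, POD 3, and POD 5". The abstract repeats the choice between t-test and Mann-Whitney.

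**The concern.** Two endpoints at five times give 2 × 5 = 10 primary comparisons, plus the area under the curve. Each passes through a pre-test on about 28 to 31 values per arm. A pass gives a difference in means. A failure gives a rank comparison with no stated effect estimate. Which of the two the trial will report is not known beforehand, and it need not be the same at POD1 as at POD2 for the same endpoint.

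This was foreseeable. By the formulas in the Primary endpoints section, HOMA-IR is a product and HOMA-β a ratio of quantities that are normally positive, so right skew is likely and a scale could have been chosen beforehand.

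Multiple imputation adds a second difficulty. The pre-test can pass in one completed dataset and fail in another, and the rule does not say which test then applies. The Mann-Whitney test as named yields a statistic and a P value, and medians with IQR are not what the usual pooling rules combine.

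**Working it through.** **Inputs from the article.** 31 patients per arm and 10% dropout, so 31 × 0.9 = 27.9, about 28 evaluable; five postoperative times; HOMA-β of 87% against 47.5%; power 0.80; two-sided α 0.05.

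**Inputs assumed.** Shapiro-Wilk at the 0.05 level; the pre-test applied separately at each time; normal or lognormal data; correlation between times of 0.3 or 0.7.

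**1. The plan's own figure.** The total of 62 cannot be reproduced because no SD is stated. That is a separate matter, but solving for the SD gives a rough idea of the spread. With difference d = 87 − 47.5 = 39.5 and n = 28 per arm:

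SD = d / [(1.960 + 0.842) × √(2/n)] = 39.5 / (2.802 × 0.2673) ≈ 52.8.

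Taking 53, the coefficient of variation is 53/87 = 0.61 to 53/47.5 = 1.12. If the data are lognormal, log-SD = √ln(1 + CV²), which gives √ln(1.371) = 0.56 to √ln(2.245) = 0.90.

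**2. Chance that the five times of one endpoint do not all get the same test.** Simulated with 500 trials per setting; ranges cover 28 or 31 per arm and both correlations.

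| Log-SD | Share of times sent to Mann-Whitney (pre-test by arm) | Mixed tests, pre-test by arm | Mixed tests, arms pooled |
|---|---|---|---|
| 0 (exactly normal) | 9-11% | 39-42% | 21-25% |
| 0.2 | 33-37% | 74-88% | 72-87% |
| 0.3 | 57-61% | 82-91% | 74-89% |
| 0.4 | 77-82% | 56-70% | 41-54% |
| 0.5 | 90-93% | 29-36% | 14-22% |
| 0.7 | 99-100% | 2-5% | 0-1% |
| 1.0 | 100% | 0% | 0% |

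Further runs at 28 per arm gave about 15% mixed at log-SD 0.6 and about 2% at 0.75.

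A hand check: if the times were independent and each failed with probability p, the chance of a mix would be 1 − p⁵ − (1 − p)⁵. At p = 0.57 this is 1 − 0.060 − 0.015 = 0.925; at p = 0.91 it is 1 − 0.624 − 0.000 = 0.376. The simulated values at 28 per arm and correlation 0.3 are 0.91 and 0.36, slightly lower as correlation would make them.

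**3. Imputation.** With 31 per arm, 10% of values missing at random and 20 imputations from a normal model within arm (all assumed), the pre-test disagreed between imputed sets of the same trial in 52%, 45% and 32% of 300 trials at log-SD 0.3, 0.4 and 0.5. Another imputation model would change these shares.

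**4. Error rate and power.** With identical distributions in both arms, the two-stage procedure rejected in 0.050 to 0.053 of trials at a single time point. Against a t-test on logs in lognormal data it lost about 0 to 3 points of power.

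**The case against.** The strongest reply has four parts.

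- *Mixing may hardly occur.* A reader might infer that the time points will be analysed on different scales. The documents do not support that. They give no SD, and the SD implied by the sample size, read as lognormal, puts log-SD at about 0.56 to 0.90. Over most of that range mixing is uncommon. This stands, so the right word is \"can\". It does not rescue the rule, because in that range nearly every time point goes to a rank test with no named effect estimate.
- *A rank test can be pooled.* A reader might infer that Mann-Whitney leaves nothing to combine over imputations. That is too strong: a Hodges-Lehmann shift or the Mann-Whitney probability, with a standard error, could serve. The plan names neither.
- *The choice is not opportunistic.* A reader might infer that the analysis is picked after looking at the outcomes. The rule is prespecified and the analyst is masked to allocation, and no material inflation of type I error was found. The choice depends on the data, but it leaves little room to favour a result.
- *This is detail for a statistical analysis plan.* That is fair for the imputation model and the pooling rule taken alone, and their absence is not the point here. The pre-test itself is stated in the article and applied to the primary endpoints, so it is a rule fixed badly and not one left out.

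The area under the curve is a single quantity per score, so mixing over times does not touch it. Its effect measure still depends on the pre-test.

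**Conclusion.** The concern holds in a limited form. The article lets the trial data decide whether each primary HOMA comparison is a difference in means or a rank test, so the effect measure is not fixed in advance. The chance of mixed tests within one endpoint depends on an unknown spread: about 80-90% at log-SD 0.3 with the pre-test run by arm, about 15% at 0.6 and about 2% at 0.75. These shares rest on lognormal data, a 0.05 pre-test level and a separate pre-test at each time, none of which the article states. Combining the rule with multiple imputation leaves open which test applies when imputed sets disagree and what is pooled on the Mann-Whitney branch.

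No bias or excess of false positives is shown. The loss is in coherence and interpretability, plus about 0-3 points of power if the data are lognormal. The power figure uses the setting that most favours the log analysis, so it should be claimed only as a modest gain. The point is worth correcting before analysis but does not threaten the trial's validity.

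**What to change.** - Drop the Shapiro-Wilk choice for HOMA-β, HOMA-IR, their areas under the curve and the skewed secondary markers (cytokines, hs-CRP, cortisol).
- Analyse each on the log scale in a linear model with treatment group. For the HOMA endpoints and areas, add the log of the admission value, which is already collected.
- Report geometric mean ratios with 95% CI whatever the distribution looks like, and pool the treatment coefficient over imputations by Rubin's rules.
- State in advance how HOMA-β is handled when glucose is at or below 3.5 mmol/L. Its denominator is then zero or negative, so the logarithm does not exist.
- Keep Mann-Whitney as a sensitivity analysis.

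The cost is wording only: no added patients, visits or assays. The downside is that results are stated as ratios and not as differences, which some clinical readers will find less familiar.
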